### Aims

2.1

The objective of current project is to establish the effectiveness of NITESGON in decreasing ALF in individuals with aMCI. Our primary hypothesis is that participants that receive active NITESGON while learning a word association task will perform better on word recall 7 and 28 days after NITESGON in comparison to control groups. In addition, we hypothesize that active NITESGON will significantly increase gamma oscillations within the medial temporal cortex after NITESGON in association with memory performance in individuals with aMCI 7 and 28 days after NITESGON.

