#### Secondary outcome measures

2.7.2

(1)Neurophysiology. Rest-state EEG will be collected immediately before and after NITESGON (T0) and will be correlated with the recall of the word-association task 7 (T1) and 28 (T2) days after NITESGON.(2)TES Adverse events*.* We will use the NITESGON exit questionnaire developed by Brunoni et al. [21] to assess potential side-effect (headache, neck pain, scalp pain, tingling, itching, burning sensation, skin redness, sleepiness, trouble concentrating, mood changes) at the end of T0.(3)Blinding. At the end of the experiment (T2), subjects will be asked if they thought they were assigned to the control or active group.(4)Control assessments. We will collect the California Verbal Learning Test II, Delis Kaplan Color Word Interference Test, Beck Depression (BDI) and Anxiety Inventory (BAI), Trial A & B, COWAT and DIGIT Span to verify that the effect obtained cannot be associated due to differences between groups on these control measures. These will be collected during visit 1 before NITESGON (T0), and 28 days after NITESGON (T2).

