### Sample size

2.9

The study is designed to give us adequate power to detect clinically meaningful differences between the groups. We plan to oversample to a target sample size of 25 subjects per group, with an overall sample of 100 subjects, to assure that our power to detect effects is maintained.

Nineteen individuals per group (total n = 76) would offer us a power of 90% to detect the difference between groups using Cohen's d estimation of a medium effect size (0.20). A sample size of 76 would allow us to see a medium effect size, however the trial is longitudinal which could increase its drop-out rate. Although we do not expect attrition to be large, we expect a dropout rate of no more than 20%. Therefore, an overall sample of 100 subjects will assure enough power to accommodate for the expected drop-out rate.

An intention-to-treat and per-protocol analysis will be performed. For the intention-to-treat analysis, the patient must successfully complete T0 and T1 assessments. For missing observations, the LOCF approach will be used. Exclusion from the population will be finalized prior to database lock in a blinded manner.

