### Statistical analysis

2.10

For our calculations, we will use the normal distribution assumption, which we will test using a normal plot and goodness of fit test. If violations are found, non-parametric tests or transformations will be utilized. Variance equivalence will be tested using the F-test. Our protocol is designed to assure sample independence, and adherence will be closely monitored. Before beginning the main statistical analyses, screening variable levels (e.g., age, sex, education, disease onset, mood) across groups will first be considered to assess group equivalence. If the groups are not balanced on any baseline characteristics, these factors will be considered as co-variate in later multivariate regressions.

The efficacy of NITESGON will be assessed on word recall by testing its effect on the mean change over time relative to the control groups. Memory task performance will be analyzed over time at baseline, and 7 and 28 days after NITESGON, and across groups. Statistically, these tests will be single degree-of-freedom interaction contrasts from a general mixed linear model containing both within- and between-subject variance components. All tests will be based on directional hypotheses in favor of improvements due to NITESGON on the behavioral assessment. We expect large behavioral effects based on our previous studies in control and patient populations.

*EEG.* sLORETA statistical contrast maps between pre and post NITESGON will be calculated for the sham and active groups through multiple voxel-by-voxel comparisons in a logarithm of F-ratio [27]. Statistical analysis is based on estimating, via randomization, the empirical probability distribution for the max-statistic under the null hypothesis comparisons [28]. This methodology corrects for multiple testing (i.e., for the collection of tests performed for all voxels and for all frequency bands). Due to the non-parametric nature of the method, its validity does not rely on any assumption of Gaussianity [28]. A comparison will be made between the contrast map for the active and sham group. The significance threshold is based on a permutation test with 5000 permutations. In addition, the statistical contrast map (pre-post) will be correlated with the difference on in memory improvement.

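### The EEG–memory correlation is specified on arm-level pre-post maps and cannot be run that way; the active–sham EEG comparison can be valid, but would be better made on participant-level values adjusted for the pre-stimulation EEG

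*Protocol article*

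**What the plan says.** The EEG paragraph of section 2.10 (Statistical analysis) starts from maps made per arm: "sLORETA statistical contrast maps between pre and post NITESGON will be calculated for the sham and active groups", expressed as the logarithm of an F-ratio at each voxel. Two further steps use these maps. The first is the arm comparison: "A comparison will be made between the contrast map for the active and sham group". The second is the link to memory: "the statistical contrast map (pre-post) will be correlated with the difference on in memory improvement".

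The same paragraph gives a basis for inference: "Statistical analysis is based on estimating, via randomization, the empirical probability distribution for the max-statistic under the null hypothesis comparisons". Directly after naming the arm comparison it adds: "The significance threshold is based on a permutation test with 5000 permutations". It does not say what is permuted.

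Section 2.7.2 (Secondary outcome measures) describes the memory link differently. There, resting EEG recorded before and after stimulation "will be correlated with the recall of the word-association task 7 (T1) and 28 (T2) days after NITESGON". Section 2.1 (Aims) gives the hypothesis that both steps serve: "active NITESGON will significantly increase gamma oscillations within the medial temporal cortex after NITESGON in association with memory performance". Section 2.9 (Sample size) plans a "target sample size of 25 subjects per group, with an overall sample of 100 subjects".

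**The concern.** A log F-ratio map calculated for an arm is a summary statistic: one number per voxel and frequency band for the whole arm. The variation between participants has been absorbed into it. That raises two questions.

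- **Correlation.** A correlation needs one EEG value and one memory value for each participant. An arm-level map supplies no participant's EEG value.
- **Arm comparison.** Two arm-level maps set side by side have no error term of their own for their difference. Whether the comparison is a proper test depends on what the permutations shuffle. Swapping pre and post within an arm tests change in that arm, not active against sham.

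At stake is the EEG hypothesis in section 2.1, that medial temporal gamma rises under active stimulation and is associated with recall. If the analysis is settled only once the maps have been seen, the choice of EEG summary, memory variable and permutation scheme remains open when the results are known.

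**Working it through.** The plan gives no figure for this point, so there is none to reproduce.

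**1. The correlation.** The two descriptions differ in both variables:

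| | EEG variable | Memory variable |
|---|---|---|
| Section 2.7.2 | resting EEG before and after stimulation | recall at T1 (day 7) and T2 (day 28) |
| Section 2.10 | statistical contrast map, pre-post | a difference in memory improvement |

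With 25 participants per arm (section 2.9), active and sham together give 2 × 25 = 50 recall scores at each visit. The maps give 2 EEG values at each voxel, one per arm. Those cannot be paired with 50 scores. Correlating the 2 arm values with the 2 arm means of recall would put two points on a line and give +1 or −1 whatever the data (unless the values tie). So no meaningful correlation follows from the section 2.10 wording. The section 2.7.2 wording reads naturally as one EEG value per participant.

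**2. The arm comparison, if arm labels are permuted.** This was simulated with 25 participants per arm. Assumptions: 200 voxels with correlation 0.5, Gaussian changes, and one t-map per arm standing in for the log F-ratio map. The statistic was the maximum absolute difference between the two arm maps. Arm labels were shuffled across participants and both maps recomputed (400 permutations; 1000 simulated trials for type I error, 400 for power).

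| Scenario | Difference of arm-level statistic maps | Difference of mean participant change maps |
|---|---|---|
| No change in either arm | 0.048 | 0.046 |
| Same change in both arms (0.5 SD in 10 voxels) | 0.052 | 0.050 |
| Power, 1-SD shift in 10 voxels | 0.91 | 0.935 |

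The simulation error of a rate near 0.05 is √(0.05 × 0.95 / 1000) ≈ 0.007, so all four type I rates agree with 0.05. The spread between participants enters through the reshuffling, even though the statistic is built from one map per arm.

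**3. The arm comparison, if each arm is tested separately.** Suppose both arms have the same true pre-post change, and each within-arm test has probability p of being significant. The arms are independent, so the chance that active is significant and sham is not equals p(1−p):

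- p = 0.05 (no change in either arm): 0.05 × 0.95 = 0.0475
- p = 0.2 or 0.8: 0.2 × 0.8 = 0.16
- p = 0.5: 0.5 × 0.5 = 0.25, the maximum

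The excess over 5% therefore needs a shared non-zero change as well as this way of reading the maps.

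**4. Gain from adjusting for the pre-stimulation value.** Let the pre and post values have equal variance σ² and correlation r. The variance of a change score is 2σ²(1−r). The variance of the post value after adjustment for the pre value is σ²(1−r²). The ratio is (1−r²) / [2(1−r)] = (1+r)/2.

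| r (assumed) | Ratio | Reduction in variance |
|---|---|---|
| 0.5 | 0.75 | 25% |
| 0.7 | 0.85 | 15% |
| 0.9 | 0.95 | 5% |

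The document gives no r.

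**The case against.** A reader might infer that neither EEG analysis can be validly tested as written. For the arm comparison the document does not support that. The permutation threshold comes in the sentence right after the comparison of the two maps, and its natural reading is that the threshold applies to that comparison. Step 2 shows that a map-against-map comparison holds its error rate when arm labels are shuffled. This part of the objection stands in full.

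A reader might also take 25% as the plan's false-positive rate. The document nowhere says that a treatment effect will be inferred from significance in one arm and not in the other. The figure is an upper bound under a procedure that the text neither states nor rules out.

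The article is also condensed. The permuted unit is the kind of detail that a full protocol or analysis plan may hold, so its absence alone would not be a finding. That stands as well. It does not remove the correlation problem, where the article states a specific procedure that cannot be carried out and that disagrees with its own outcome section.

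It can be said that no analyst would attempt a correlation on one map per arm, so the sentence is only loose shorthand. That is probably true, and it limits the harm. It still leaves the EEG value and the memory variable to be chosen later.

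Finally, a pre-post contrast is valid in a randomised comparison, and baseline adjustment adds precision, not validity. That is correct, and the adjustment is recommended here on precision alone.

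**Conclusion.** The point holds in a limited form.

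- **Correlation:** it cannot be run as section 2.10 words it, and it must be reconciled with section 2.7.2. This rests on the text alone.
- **Arm comparison:** it is valid if the permutations shuffle arm labels across participants (simulated type I error 0.048 to 0.052, under the assumptions listed). It would be invalid only if separate within-arm verdicts were compared; the chance of a false claim would then be p(1−p), at most 25%, given the same non-zero change in both arms. The text does not settle which is meant.
- **Better method:** a participant-level analysis adjusted for the pre-stimulation EEG serves both steps and is more precise than a change score, by 5% to 25% of the variance for r from 0.9 to 0.5, assuming equal pre and post variances.

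The change is worth making because it settles the analysis before the data are seen. It concerns a secondary outcome and does not touch the primary recall analysis.

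**What to change.** Reword the EEG paragraph of section 2.10 as follows, and bring section 2.7.2 into line with it.

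1. For each participant, compute log gamma current density before and after stimulation, in the medial temporal cortex or per voxel.
2. Compare active with sham on the post value adjusted for the pre value. State that the 5000 permutations shuffle arm labels across participants, keeping each participant's pre and post values together. If the analysis is per voxel, keep the max-statistic correction.
3. Correlate the same participant-level EEG value (post adjusted for pre) with that participant's recall at T1 and at T2, and use the same memory variables in both sections.
4. Report the within-arm pre-post maps as description only.

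The cost is analysis wording only: the pre- and post-stimulation EEG is already collected, and the number of permutations stays the same.

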In a recent study we demonstrated that non-invasive transcutaneous electrical stimulation of greater occipital nerve (NITESGON) improves memory in healthy young (18–25 years) [15] and older (>65 years) [16] participants up to 28 days after stimulation. In the latter study, NITESGON was utilized in an older population to determine if stimulation during an associative memory task can optimize associative memory performance up to 28 days later. Thirty subjects between the ages of 55 and 70 years were enrolled and randomly assigned to active or sham NITESGON group. Active or sham NITESGON was delivered during the study phase at visit 1 of the associative memory task, and participants were asked to return 7-and 28-days later to measure memory recall. During visit 1, participants learned a list of 50 Swahili-English word pairs (e.g., mashua-boat) across a total of 3 blocks for each study (S) and test (T) phase. The study phase of each block consisted of 50-word pairs followed by a test phase of the 50 words, in which participants were asked to type the correct English translation for each Swahili word. Participants were then dismissed and returned for the test 7-days and 28-days later (recall phase). During this test, subjects were shown each Swahili word and were asked to type the correct English translation. This was identical to the test phase from the first visit. Participants that received active stimulation exhibited increased words recalled on days 7 and 28 compared to participants that received sham stimulation (Day 7: η^**2**^ = .21; Day28: η^**2**^ = .14). These findings suggest that NITESGON enhances memory performance up to 28-days after a single session. With these results, we propose that NITESGON could mitigate memory loss and rate of decline in the earliest stages of Alzheimer's disease.

Results also demonstrated that NITESGON promotes noradrenaline (NA) release though LC activation, followed by enhanced communication between the LC and hippocampus. NITESGON induced synaptic plasticity then modulates memory with lasting effects by strengthening memory consolidation after encoding, resulting in upregulated memory performance [15]. Furthermore, we were able to show that NITESGON induces gamma changes in the medial temporal lobe immediately after NITESGON, which was correlated with successful recall several days after stimulation. This latter finding suggest that gamma oscillations can potential be use as a biomarker for successful recall.

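### The EEG–memory correlation is specified without treatment arm; if active and sham participants are analysed together, the predicted arm differences alone make it reject too often

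*Protocol article*

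**What the plan says.** The protocol article describes this analysis twice. Under Secondary outcome measures (2.7.2), resting EEG recorded before and after stimulation "will be correlated with the recall of the word-association task 7 (T1) and 28 (T2) days after NITESGON". Under Statistical analysis (2.10), the EEG paragraph has three steps:

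1. "sLORETA statistical contrast maps between pre and post NITESGON will be calculated for the sham and active groups".
2. "A comparison will be made between the contrast map for the active and sham group".
3. "the statistical contrast map (pre-post) will be correlated with the difference on in memory improvement".

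Steps 1 and 2 name the arms. Step 3 does not: it has no arm term, no stratification, no restriction to one arm, and no statement of which participants enter. The sentence in 2.7.2 is silent on the same points.

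The Aims (2.1) state both arm effects. Active participants "will perform better on word recall 7 and 28 days after NITESGON in comparison to control groups", and "active NITESGON will significantly increase gamma oscillations within the medial temporal cortex after NITESGON in association with memory performance". The end of the Background also says that this trial will examine how medial temporal gamma is associated with memory performance.

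**The concern.** The question is about individuals: do participants with a larger gamma change recall more words? A plain correlation across participants from more than one arm tests a different null hypothesis, namely zero correlation overall. Overall correlation has two sources, the association within arms and the difference between arm means. If stimulation raises both gamma and recall, the second source is positive even when the first is zero. The test then partly detects the treatment effect again.

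At stake is the trial's mechanistic reading. A link between gamma and recall could be reported when none exists within either arm, and the risk grows with the size of the treatment effects that the trial hopes to see. This holds whether the memory variable is recall at day 7 or 28, as in 2.7.2, or an improvement score, as in 2.10.

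**Working it through.** The article gives no figure for this correlation, so there is none to reproduce.

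**Inputs**
- Recall effect: the Background reports, for the earlier active-versus-sham study in older adults, "Day 7: η^2^ = .21; Day28: η^2^ = .14". For two equal arms, d = 2·√(η²/(1−η²)). Day 7: 2·√(0.21/0.79) = 1.03. Day 28: 2·√(0.14/0.86) = 0.81.
- Gamma effect: not given in the document. Assumed, d = 0 to 1.03.
- Participants: 25 per arm (2.9). With the 20% dropout allowed there, 25 × 0.8 = 20 per arm.
- Significance level: none is stated for this test. Two-sided 5% is assumed.
- Correlation within each arm: set to zero, so every rejection is false for the association question.

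**Correlation created by pooling.** With a share p of participants in the active arm and arm shifts d_g (gamma) and d_m (recall) in within-arm standard deviations,

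ρ = p(1−p)·d_g·d_m / √[(1 + p(1−p)·d_g²)(1 + p(1−p)·d_m²)].

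For active plus sham, p(1−p) = 0.25. At d_g = d_m = 1.03, 0.25 × 1.03² = 0.265, so ρ = 0.265/1.265 = 0.21. At d_g = 0.5 and d_m = 0.81, the numerator is 0.25 × 0.5 × 0.81 = 0.101 and the denominator is √(1.0625 × 1.164) = 1.112, so ρ = 0.09.

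**Rejection rate.** Simulated trials with bivariate normal data, one EEG region and 25+25 participants, comparing a Pearson test without arm with a partial correlation after centring both variables within arm (10,000 trials per setting):

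| Assumed gamma d | No arm term, recall d 0.81 | No arm term, recall d 1.03 | Arm-adjusted |
|---|---|---|---|
| 0 | 5% | 5% | 5% |
| 0.2 | 5.6% | 5.8% | 5% |
| 0.5 | 9.6% | 12.2% | 5% |
| 0.8 | 16.4% | 22.4% | 5% |
| 1.0 | 21.4% | 30.1% | 5% |

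With both effects at 1.03 the unadjusted rate is about 32%. With 20+20 it runs from about 8% to 26% for gamma d from 0.5 to 1.03. A correlation computed in the active arm alone also stays at about 5% in every setting.

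**What adjustment costs in power.** A true within-arm correlation of 0.4 with 25+25 is still detected about 83% of the time after adjustment for arm (two-sided 5%).

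**The case against.** **Pooling is not stated.** Maps are built for the sham and active groups, the between-arm comparison is a separate step, and the last sentence correlates the pre-post map. A correlation within each group, or within the active group only, fits those words, and it has no such problem. This stands. A reader might infer that the article commits the trial to a pooled, confounded test, but the text does not go that far. It names a plain correlation directly after analyses that involve both arms and does nothing to exclude the pooled version.

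**A condensed article may leave this detail to the full protocol or SAP.** True of much detail. Here, however, the article itself sets out the method, the multiplicity correction and the number of permutations. Whether the correlation is conditional on arm decides which question it answers.

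**The size rests on an assumed gamma effect.** This stands. At gamma d = 0.2 the rate is close to nominal, and at zero there is no inflation. The recall effects come from healthy older adults, not people with aMCI. A reader might also infer that the test will reject whenever both arm effects exist; in every setting above it fails to reject in most trials.

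**One region is not the planned voxel-wise analysis.** This stands as to the size: if the max-statistic correction also covers the correlation, the rates will differ. It does not remove the mechanism, because that correction handles multiplicity over voxels and bands, and permuting freely across arms still tests overall independence.

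**The biomarker claim belongs to the earlier study.** This also stands. The remark that "gamma oscillations can potential be use as a biomarker for successful recall" interprets previous results, and a reader who infers that this trial has committed itself to a biomarker conclusion goes beyond the text. What the trial does commit to is an association between gamma and memory performance, and that is enough for the point.

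**Conclusion.** The point holds in conditional form. The analysis is written as a plain correlation with no arm term and no within-arm restriction. If active and sham participants are analysed together, the arm shifts predicted in the Aims inflate the rejection rate for the association question. For one region at two-sided 5% with 25+25, it rises from 5% to about 6% at gamma d = 0.2, 10–12% at 0.5, 16–22% at 0.8 and up to 32% at 1.03.

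These figures assume normal data, no association within arm, recall effects as large as in the earlier study, and a gamma effect that the document does not give. If the correlation is run within arm, there is no inflation. The analysis is secondary and the primary recall contrasts are untouched. The change is still worth making, because it settles the ambiguity and is nearly free.

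**What to change.** In 2.10, replace the correlation sentence with one that names the arms entering the analysis and makes it conditional on arm: regress recall on EEG change with arm as a factor or, equivalently, centre both variables within arm and correlate the residuals. If the voxel-wise permutation test is used for this step, permute within arm. Align the sentence in 2.7.2. Report the active-arm correlation and the arm-by-EEG interaction descriptively, and base any statement linking gamma to recall on the arm-adjusted estimate.

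No new data are needed. The cost is one degree of freedom per arm term (one for active and sham, three if all four arms enter) and a smaller reported correlation whenever part of the unadjusted one is the arm difference.

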### Study design

2.3

This study is designed as a prospective, double-blind, placebo-controlled, randomized parallel-group study that will be completed at Trinity College Dublin, Ireland. A total of 100 individuals with amnestic mild cognitive impairment (aMCI) based on diagnostic criteria described by the National Institute on Aging and Alzheimer's Association [17] will be recruited from Alzheimer's Ireland. Subject will receive a (real or control) non-invasive transcutaneous electrical stimulation of the greater occipital nerve (NITESGON) procedure. After providing written informed consent, subjects will be assigned to one of four groups. One group will receive active NITESGON, while the three groups will be control groups. One group will receive sham NITESGON (inactive control), while a second group will receive active NITESGON with local anesthesia (active control; local nerve anesthesia group) and a third group will stimulate the C5/C6 nerve (active control; same sensation different nerve). We will include three control groups so that we are able to verify that the effect is real, location specific and cannot be associated to a sensation effect.

We have opted to use a parallel-group design as it is unclear what the carry-over effect and/or wash-out period will be for NITESGON. Subjects will be randomized after screening evaluation and will be assigned to receive one of the four possible types of NITESGON. To eliminate subjective bias, all subjects and the investigator testing the endpoint measures will be blinded to the type of intervention. The researcher who will control the NITESGON device will not be involved in instructing the participant; this will be performed by a second researcher who will be blind to the stimulation protocol. The primary outcome will be change in memory performance as measured by a word association task, measured at baseline (T0), 7 days after NITESGON (T1) and after 28 (T2) days after NITESGON. Secondary outcomes include changes in resting EEG, which will be assessed immediately before and after NITESGON (see Fig. 1 and Table 1).

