### Study procedure

2.5

We will conduct this study as follows:(1)Screening of individuals with aMCI.(2)Randomly assigning aMCI subjects to one of the four NITESGON groups.(3)Administering one session of 1.5-mA active (*n* = 25) or control (*n* = 25 in each of three control group) NITESGON paired with a word-association task; administered by research assistant.(4)Behavioral assessments after each of the three blocks of studying the word associations and neural measures immediately after the last session of Behavioral assessments (T0).(5)Behavioral assessments at seven (T1) and 28 (T2) days after NITESGON.

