### Intervention

2.6

NITESGON will be delivered by a specially developed, battery-driven, constant current stimulator with a maximum output of 10 mA (http://www.neuroconn.de) via a pair of saline-soaked surface sponges (35 cm^2^) on the scalp. One electrode will be placed over the left and right C2 dermatomes each. A constant current of 1.5 mA intensity will be applied during each of the 3-study phases (i.e., 250 s x 3 blocks). For sham NITESGON, placement of the electrodes will be identical to active NITESGON. A third group (local nerve anesthesia group) will receive NITESGON, but we will use a topical skin anesthetic (lidocaine/prilocaine cream) to reduce any potential contribution from transcutaneous stimulation of peripheral nerves. This lidocaine/prilocaine preparation blocks sodium channels in peripheral nerves in the skin and thereby stabilizes the membrane potential and increases the threshold for firing an action potential [15,19]. For the fourth control group (different nerve group), the electrodes will be placed over cervical nerves five and six, to mimic the sensation, but change the location. For both the third and fourth control group, we will apply the same current as active NITESGON. NITESGON will first be switched on in a ramp-up fashion over 30 s. For sham, the current intensity (ramp down) will gradually be reduced (over 5 s) as soon as NITESGON reaches a current flow of 1.5 mA. The rationale behind this sham procedure is to mimic the transient skin sensation at the beginning of active NITESGON without producing any conditioning effects on the brain.

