*TES Adverse events.* A comparison will be conducted between the active and sham group using a one-way ANOVA with stimulation (active NITESGON vs sham NITESGON) as independent variable and adverse events as dependent variable.

*Blinding.* A Chi-square test will be conducted comparing actual stimulation (active NITESGON vs sham NITESGON) versus participants' expected stimulation (active NITESGON vs sham NITESGON).

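### The adverse-event comparison covers only active versus sham, so the anaesthesia and C5/C6 arms enter no planned between-group comparison and the sensation premise of those controls goes untested

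*Protocol article*

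**What the plan says.** For adverse events, section 2.10 fixes both the test and its groups: "A comparison will be conducted between the active and sham group using a one-way ANOVA with stimulation (active NITESGON vs sham NITESGON) as independent variable". The blinding test in the same section uses the same two groups.

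Section 2.6 describes what each arm receives:
- Anaesthesia and C5/C6 arms: "For both the third and fourth control group, we will apply the same current as active NITESGON".
- Sham arm: "For sham, the current intensity (ramp down) will gradually be reduced (over 5 s) as soon as NITESGON reaches a current flow of 1.5 mA".
- Anaesthesia arm, in addition: "we will use a topical skin anesthetic (lidocaine/prilocaine cream) to reduce any potential contribution from transcutaneous stimulation of peripheral nerves".
- C5/C6 arm: electrodes at a different site, chosen so that the stimulation feels alike.

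Section 2.3 explains that three control groups are included in order to "verify that the effect is real, location specific and cannot be associated to a sensation effect", and labels the C5/C6 arm as the control with the same sensation on another nerve.

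Section 2.7.2 collects an exit questionnaire at the end of T0. Its items include "headache, neck pain, scalp pain, tingling, itching, burning sensation, skin redness". No restriction by arm is stated. Section 2.11 adds, as a general statement, that every variable will be summarised and reported.

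**The concern.** The comparison is narrower than the exposure. Two control arms receive the full current, and each carries something the active arm does not: anaesthetic cream in one, a different electrode site in the other. The reassurance in section 2.8 about side effects rests on earlier comparisons of active with sham NITESGON and does not reach these two conditions.

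The larger consequence is for interpretation. The two active controls support the specificity claim only if they did what they were designed to do. If C5/C6 stimulation felt clearly different from active stimulation, a recall difference between those arms could still be a sensation effect. If the cream made no difference to what participants felt, the anaesthesia arm would be harder to interpret. The tingling, itching, burning and pain items are the only described data that bear on this, and no planned comparison uses them for it. The blinding test does not fill the gap, because it also stops at active versus sham.

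**Working it through.** **Inputs.** Allocation is 25 active and 25 in each of three control groups (section 2.5); section 2.9 confirms a "target sample size of 25 subjects per group, with an overall sample of 100 subjects". Current by arm is from section 2.6. The groups compared are from section 2.10.

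**Step 1: count who is in the comparison.**

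| Arm | n | Sustained 1.5 mA | In the adverse-event comparison |
|---|---|---|---|
| Active | 25 | yes | yes |
| Sham | 25 | no | yes |
| Anaesthesia | 25 | yes | no |
| C5/C6 | 25 | yes | no |

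Total: 4 × 25 = 100, which reproduces the stated target. Sustained current: 3 × 25 = 75. Exposed but outside the comparison: 2 × 25 = 50. Share of those exposed: 50/75 = 66.7%. Share of all participants: 50/100 = 50%.

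**Step 2: match each design premise to a planned test.**

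| Premise | Comparison that would check it | Planned? |
|---|---|---|
| C5/C6 feels like active (2.3, 2.6) | active vs C5/C6, sensation items | no |
| Cream reduces peripheral nerve input (2.6) | active vs anaesthesia, sensation items | no |
| Active is tolerated like sham (2.8) | active vs sham, all items | yes |

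**Step 3: would pooling all exposed arms against sham be a good replacement?** Two-sided exact Fisher power at the 5% level, with assumed symptom rates (the article gives none):
- Active 40% vs sham 10%, 25 vs 25: 59%.
- All three current arms at 40% vs sham 10%, 75 vs 25: 84%.
- Active 40%, C5/C6 40%, anaesthesia 10%, sham 10%, pooled 75 vs 25: about 50%. The pooled rate is then (40 + 40 + 10)/3 = 30%.

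The gain from 59% to 84% needs equal rates in the three current arms. If the cream lowers the symptom rate to the sham level, pooling does worse than the planned comparison.

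**Step 4: what can 25 per arm show about similarity?** If the true rate is 40% in both active and C5/C6 (assumed), the approximate 95% half-width for the difference is 1.96 × √(2 × 0.4 × 0.6/25) = 1.96 × 0.139 = 0.27, or 27 percentage points. For a graded score, the difference detectable with 80% power at 25 vs 25 is 0.81 standard deviations (two-sided 5% t-test). A non-significant difference would therefore not show that the sensations match; the estimate and interval must be shown.

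**The case against.** Active versus sham is a defensible main tolerability contrast. Active NITESGON is the intervention proposed for use, and the cream and C5/C6 arms are mechanistic controls. The article offers the questionnaire as a side-effect measure and never claims that it verifies sensation matching, so leaving out that check contradicts nothing and does not change the primary recall contrasts. This stands, and it is why active versus sham should stay as the main contrast.

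Four stronger readings are tempting, and the article does not support them.
- *The control-arm data go unused, or a reaction confined to one of those arms could not be seen.* The questionnaire is collected without restriction by arm and section 2.11 promises summaries of all variables, so such a reaction could appear descriptively. That sentence is generic and does not promise results by arm; tabulation detail may sit in a fuller document that is not shown.
- *Safety information on two thirds of those exposed is lost.* The chance of observing a rare event depends on how many people are asked, not on which arms enter the test. Nothing in the article limits the questionnaire to the two compared arms.
- *All 75 exposed participants should be pooled against sham as the main test.* Pooling assumes equal symptom rates in the three current arms, which conflicts with the purpose of the cream.
- *ANOVA is simply the wrong test.* Section 2.10 allows non-parametric tests or transformations if normality fails, so this is at most secondary.

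What remains is that section 2.10 states a two-group rule in a four-arm trial, and that rule leaves a stated purpose of two arms without a check.

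**Conclusion.** The point holds as a gap in the planned comparisons, not as a loss of data. Fifty of the 75 participants given sustained current (67%) are in no planned between-group adverse-event or sensation comparison, and neither sensation-related premise of the active controls is tested. The count rests only on the stated allocation and the stated current by arm; it depends on no power figure and no assumed event rate. The rates in the pooling and precision calculations are assumptions, used only to choose the form of the fix.

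The primary recall analysis is unaffected. What is weakened is the support for saying that a recall effect is not a sensation effect. One limit applies: the questionnaire measures felt symptoms, so for the cream it is an indirect check on nerve input. The change is worth making because it is cheap and amends a rule the article states explicitly.

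**What to change.** In section 2.10, under adverse events:
1. Report each listed symptom for all four arms: number, percentage and exact confidence interval.
2. Keep active versus sham as the main tolerability contrast.
3. Add two manipulation checks on the tingling, itching, burning and pain items: active versus C5/C6, and active versus anaesthesia. Give the estimated difference with its interval, and say that a non-significant result will not be read as proof of equal sensation.
4. Do not make a pooled comparison of all current-exposed participants with sham a main analysis.

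Cost: revised analysis wording, some table columns and a few extra secondary comparisons, which should be labelled as such. The questionnaire is already described for T0 without restriction by arm, so no new data, visits or participants are needed.
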